## Abstract

Colorectal cancer (CRC) is the third most common cancer and the second cause of cancer death worldwide. Several factors have been postulated to be involved in CRC pathophysiology, including heritable and environmental factors, which are the latest to be closely associated with nutritional habits, physical activity, obesity, and the gut microbiota. The latter may also play a key role in CRC prognosis and derived complications in patients undergoing surgery. This is a single-center, open, controlled, randomized clinical trial, in patients with scheduled surgical intervention for CRC. The primary objective is to assess whether a pre-surgical nutritional intervention, based on a high-fiber diet rich in polyunsaturated fatty acids (PUFAs), can reduce disturbances of the gut microbiota composition and, consequently, the rate of post-surgical complications in patients with CRC. Patients will be randomized in a 1:1 ratio after receiving a diagnosis of CRC. In the control arm, patients will receive standard nutritional recommendations, while patients in the intervention arm will be advised to follow a high-fiber diet rich in PUFAs before surgery. Participants will be followed up for one year to evaluate the overall rate of postsurgical complications, recurrences of CRC, response to adjuvant therapy, and overall/disease-free survival.

## 1. Introduction

The gut microbiota comprises a community of about 100 trillion microbes, including bacteria, viruses, and yeasts, that have a symbiotic and mutualistic relationship with the host [1]. Although the composition of the microbiota is believed to be fairly stable in adults, it is influenced not only by host genetics, but also by environmental factors including diet, chemical exposure, and antibiotic consumption. The role of the gut microbiota in health has been extensively explored, and together with microbial-derived metabolites, they play a critical role in several physiological processes including host metabolism, immune system, and even behavior [1,2,3]. Thus, the disruption of the normal balance of gut microbiota is characterized by the depletion of commensal bacteria, overgrowth of opportunistic pathogens, and reduction in total microbiota diversity [4]. Indeed, such disturbances can lead to the development of different disorders, ranging from metabolic disturbances to cardiovascular, neurological, respiratory, and intestinal conditions, and even certain types of cancer [5].

Colorectal cancer (CRC) represents the third most common cancer worldwide and it is the second leading cause of cancer death, with an associated high economic burden [6]. The exact etiology of CRC remains unclear, although several studies have focused on the evaluation of the mechanisms involved. Most CRC cases (approximately 90%) occur sporadically (not related to the genetics of family history of the disease), and several lifestyle factors including obesity, diets with a high content of fat and (or) red and (or) processed meat, environmental pollutants, cigarette smoking, and alcohol abuse, have been associated with CRC development and progression [7]. Furthermore, there is emerging evidence that patients with CRC display significant alterations in gut microbiota, mainly characterized by an increase in opportunistic pathogens (e.g., *Enterococcaceae*, *Campylobacter*) [8] and a decrease in butyrate-producing bacteria, including *Bifidobacteria*, *Roseburia* and *Faecalibacterium prausnitzii* [9]. Overall, these alterations in the gut microbiome have been proposed to play an important role in tumor formation and progression [7,10].

Currently, surgery represents the main treatment for patients with CRC [11]. Nonetheless, major postoperative complications are not unusual in these patients. These complications include anastomotic leakage, wound infection, ileus, and bleeding, which lead to an increase in the risk of morbimortality, length of hospital stay, and re-admission, which, in turn, increases the economic burden on health systems [12]. Remarkably, the gut microbiota and related metabolites have been described as key players in postoperative recovery. For instance, commensal bacteria are known to be involved in intestinal barrier healing and barrier function [13,14]. Thus, it is not surprising that disturbances of the gut microbiota in CRC patients undergoing surgery is related to postsurgical complications.

On the other hand, certain dietary factors have been suggested to be associated with CRC incidence, tumor progression, and response to therapy [15]. For instance, higher intakes of dietary fiber, dietary calcium, and yogurt have been associated with a lower risk of CRC [15]. Thus, nutritional strategies are emerging as a promising strategy for the prevention and management of CRC. In this direction, dietary fiber has been shown to modulate the gut microbiota profile, affecting metabolic activities in the gastrointestinal tract, favoring the growth of protective bacteria [16]. Importantly, diets rich in whole grains and dietary fiber have been associated with a lower risk of developing *F. nucleatum*-positive CRC [17]. In addition to dietary fiber, recent studies have highlighted the impact of dietary omega-3 polyunsaturated fatty acids (PUFAs) on the gut microbiota [18]. Moreover, PUFAs have been demonstrated to increase the proportion of butyrate bacterial genera, e.g., *Bifidobacterium*, *Roseburia* and *Lactobacillus* [19], while reducing the number of opportunistic pathogens leading to a reduction of microbial alterations in the gastrointestinal tract [20]. However, studies relating to the modulation of gut microbiota by diet and the outcomes related to CRC surgery are still scarce. Therefore, we outline here our study protocol for a study on the impact of a pre-surgical nutritional intervention based on the intake of a high-fiber diet rich in PUFAs on disturbances of the gut microbiota, and therefore, on post-surgical complications in patients with CRC undergoing elective surgery.

## 2. Methods

### 2.1. Study Objectives

The objective of this study is to evaluate whether a pre-surgical nutritional intervention based on a high-fiber diet rich in PUFAs can revert gut microbiota alterations, surgical site infections, and anastomotic leaks in patients with CRC undergoing elective surgery (colonic resection with anastomosis), compared to a control group following standard nutrition recommendations.

To achieve this objective, three major aims are defined:To determine the change in the gut and intra-tumoral microbiome composition, fecal and serum levels of short-chain fatty acids (SCFAs), and serum inflammation, endotoxemia, and intestinal permeability markers in CRC patients following a high-fiber diet rich in PUFAs in the preoperative phase, in comparison to the control group.To evaluate the rate of anastomotic dehiscence and surgical site infections after surgery (30 days of follow-up) in the intervention group, in comparison to the control group.To establish the length of hospitalization, recurrences of CRC, response to adjuvant therapy, and overall and disease-free survival after surgery (1 year of follow-up) in the intervention group, in comparison to the control group.

### 2.2. Study Design

A single-center, parallel-arm, open, controlled, randomized clinical trial will be performed in patients with scheduled surgical intervention for CRC in the General Surgery and Digestive System Unit of the Virgen de la Arrixaca University Hospital (Murcia, Spain). All the included individuals must have passed the protocol of the Virgen de la Arrixaca University Hospital to be candidates for elective major surgery for CRC, and must sign the informed consent after being informed of the objectives and the methodology of the study.

### 2.3. Study Setting

Study subjects will be recruited in the General Surgery and Digestive System Unit of the Virgen de la Arrixaca University Hospital (Murcia, Spain) among those patients diagnosed with CRC and scheduled for elective surgery.

### 2.4. Eligibility Criteria

#### 2.4.1. Inclusion Criteria

Consecutive adult patients diagnosed with CRC and undergoing elective surgery will be eligible. The following criteria must be met for inclusion in the study:Age between 18–80 years old;After the clinical diagnosis of CRC (stage I–III), the doctor has recommended and arranged for CRC surgery.

#### 2.4.2. Exclusion Criteria

Patients who fulfill any of the following criteria will be excluded from the study:Clinical diagnosis of stage IV CRC;Current gastrointestinal illness other than gastroesophageal reflux disease or hemorrhoids;Chronic liver or kidney disease;History of cardiac disease;Positive genetic test for inherited polyposis syndromes (such as familial adenomatous polyps, hereditary non-polyposis colon cancer syndromes, etc.);Alcoholism or illicit drug use;Antibiotic use within the past 2 months;Dietary supplement use including pre- or probiotics within the past month;History of intestinal cancer, inflammatory bowel disease, celiac disease, or malabsorptive bariatric surgery;Inflammatory or connective tissue disease (such as lupus, scleroderma, rheumatoid arthritis, etc.).

### 2.5. Consent

Patient informed consent for participation will be obtained by the specialist or research nurse at the General Surgery and Digestive System Unit. A member of the team will inform patients of the objectives and methodology of the study and patients will be given a written Patient Information Sheet (Annex S1 in Supplementary Materials). Patients will be able to ask any questions regarding the Information Sheet. The Helsinki Declaration will be followed during the duration of the study.

### 2.6. Research Ethics Approval

This study will be carried out in the Virgen de la Arrixaca University Hospital in accordance with the current Spanish legislation that regulates the carrying out of biomedical research projects, for which this protocol is established as a reference document for review by the Ethical Committees, as well as for the practical decision-making in the management of included patients by participating researchers. The study has already obtained written authorization from the Research Ethics Committee (internal code 2021-2-7-HCUVA).

### 2.7. Protocol Amendments

Except for those emergency situations, no protocol changes or deviations will be allowed without documented approval. The Research Ethics Committee must be informed of possible changes and will approve in writing any change or deviation that may increase the risks of the subject and/or may adversely affect the rights of the volunteer or the validity of the research. This stipulation does not apply to those changes that are made to reduce the inconvenience or avoid risks to the subjects and to changes that would affect the administrative aspects of the study. This study will be conducted with respect for the rules of Good Clinical Practice (GCP) and the regulations and recommendations that appear in the Declaration of Helsinki and that are included in the current legislation on biomedical research at all times.

### 2.8. Intervention

Patients will be randomized in a 1:1 ratio after receiving a diagnosis of CRC during endoscopic evaluation (Figure 1). Patients included in the control arm will receive standard nutritional recommendations, while patients in the intervention arm will be advised to follow a high-fiber diet rich in PUFAs (total dietary intake of at least 30 g of fiber per day, and at least 3 g of PUFAs per day from food, not supplements) for at least 4 weeks before surgery.

Participants may withdraw or revoke consent at any time without giving explanations and without any prejudice to them. Individuals who drop out of the study will not undergo further follow-up or be replaced by new subjects. Subjects may be withdrawn if researchers/clinicians consider that the participant can no longer comply with all the requirements of the study, or if any of the procedures is considered as potentially harmful to the subject.

As this is a prospective longitudinal study, some patients might find it difficult to follow the nutritional recommendations. Nevertheless, thanks to the close monitoring of the expert nutritionist, we will manage to reduce the abandonment percentage to a minimum. We plan to provide a written protocol in lay terms for the study participants, including a detailed handbook that they can use as a guide, and they will have full access to the nutritionist via telephone or weekly individual meetings.

Participants will not be allowed to consume any dietary supplement including pre- or probiotics during the intervention period.

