### 2.12. Randomization and Blinding

Patients will be randomized in a 1:1 ratio after receiving a diagnosis of CRC in the endoscopic evaluation. In the control arm, patients will receive standard nutritional recommendations, while patients in the intervention arm will be advised to follow a high-fiber diet rich in PUFAs (total dietary intake of at least 30 g of fiber per day, and of at least 3 g of PUFAs per day from food, not supplements) at least 4 weeks before surgery. Simpler randomization will be computer-generated by a member of the study team at the site.

Given the nature of the intervention, neither patients nor research or medical staff will be blinded. Group assignment will be revealed to patients at the moment of participating acceptance.

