### 2.13. Data and Sample Collection and Analysis of Variables

#### 2.13.1. Data Collection

Data and samples will be obtained at 3 different time points: at baseline, the day before CRC surgery, and one year after surgery. For data collection, a complete clinical evaluation of the patients will be performed, which will include the registration of anthropometric data (height, weight, body mass index (BMI), waist-to-hip ratio, blood pressure), information about the patient’s medication, and assessment of dietary intake using validated food frequency questionnaires (FFQs) [21]. Baseline dietary fiber and PUFA intake will be estimated from the FFQs. All participants will be asked to complete a food diary during the 4 weeks of intervention for assessment of dietary changes.

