## 3. Discussion

To the best of our knowledge, this is the first study protocol evaluating the impact of a pre-surgical nutritional intervention based on high-fiber intake with high levels of PUFAs on altered gut microbiota and its relationship with post-surgical complications, especially anastomotic leaks and site infections. Previous studies on human subjects have demonstrated the modulation of the microbiota through dietary interventions, even in the short term [23,24,25]. In this direction, the consumption of diets rich in PUFAs have been shown to modulate the gut microbiota composition, favoring the growth of protective bacteria such as *Bifidobacteria* and *Lactobacilli*, while reducing the presence of pathobionts such as *Porphyromonas* spp. after 6 weeks of treatment [20,26,27]. Thus, our hypothesis is that the intake of a fiber-rich diet with high levels of PUFAs prior to CRC surgery could lead to a modified, more balanced gut microbiota, which could result in a lower number of complications after surgery.

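### The 3 g/day PUFA floor names no fatty-acid class, although the rationale is omega-3; read as total PUFA, it may neither separate the arms nor identify adherent patients

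*Protocol article*

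**What the plan says.** Section 2.8 (Intervention) asks the intervention arm for a daily minimum of 30 g fiber and "at least 3 g of PUFAs per day from food, not supplements". Section 2.12 (Randomization and Blinding) restates the second part as "of at least 3 g of PUFAs per day from food, not supplements". Both are absolute floors on intake, not increases over the patient's own baseline, and neither names a fatty-acid class.

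The abbreviation is introduced in two ways. The Abstract describes an intervention "based on a high-fiber diet rich in polyunsaturated fatty acids (PUFAs"), with no restriction to omega-3. The Introduction (Section 1) justifies the component by saying that "recent studies have highlighted the impact of dietary omega-3 polyunsaturated fatty acids (PUFAs) on the gut microbiota", which attaches the same abbreviation to omega-3. The Discussion (Section 3) hypothesizes about "the intake of a fiber-rich diet with high levels of PUFAs prior to CRC surgery", again without a class.

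For the comparator, Section 2.8 says: "Patients included in the control arm will receive standard nutritional recommendations". It states no PUFA content. For measurement, Section 2.13.1 says "Baseline dietary fiber and PUFA intake will be estimated from the FFQs" and "All participants will be asked to complete a food diary during the 4 weeks of intervention for assessment of dietary changes". Section 2.15 plans an intention-to-treat analysis, with a secondary per-protocol analysis of the primary outcomes among participants who met the intervention. The eligibility criteria (Section 2.4) do not use habitual fiber or PUFA intake.

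**The concern.** One abbreviation carries two meanings, and the only number that defines the PUFA component depends on which meaning applies.

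- **If omega-3 is meant**, Sections 2.8, 2.12 and 2.13.1 do not say so. A nutritionist or diary coder who follows the Abstract would count omega-6 toward the target.
- **If total PUFA is meant**, the target no longer matches the omega-3 argument. The amount is also small enough that some or many patients in either arm might reach it without changing anything.

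Three things are at stake. The first is the PUFA contrast between arms, which could be diluted. The second is the per-protocol set: the floors in Sections 2.8 and 2.12 are the only numeric definition of the intervention, so a PUFA criterion that is ambiguous or routinely met may screen out nobody, or may admit patients who changed nothing. The third is interpretation: whatever the result, it would be hard to say whether a PUFA-rich diet had been delivered and compared with something different.

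**Working it through.** **1. What can be reproduced.** The 3 g/day floor is stated without a derivation, so there is no calculation to repeat. The check is one of scale and sensitivity.

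**2. Inputs.**
- Floor: 3 g/day (Sections 2.8 and 2.12).
- Energy content of fat: 9 kcal/g (assumption; standard conversion factor).
- Daily energy intake: 1,500 to 2,500 kcal (assumption; not in the article).
- Habitual intake: not in the article. Assumed lognormal, with median m from 2 to 8 g/day and coefficient of variation (CV) 0.3 or 0.5.

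**3. Scale, if the floor means total PUFA.** Energy from the floor = 3 × 9 = 27 kcal/day.

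| Assumed energy intake | Share from 3 g PUFA |
|---|---|
| 1,500 kcal | 27/1,500 = 1.80% |
| 2,000 kcal | 27/2,000 = 1.35% |
| 2,500 kcal | 27/2,500 = 1.08% |

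**4. Share of patients already at the floor before any advice.** With σ = √ln(1 + CV²), the share is 1 − Φ[(ln 3 − ln m)/σ]. For CV 0.3, σ = √ln 1.09 = 0.294; for CV 0.5, σ = √ln 1.25 = 0.472.

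Example, m = 5 and CV 0.5: (ln 3 − ln 5)/0.472 = −0.511/0.472 = −1.08, and 1 − Φ(−1.08) = 0.86.

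| Assumed median | CV 0.3 | CV 0.5 |
|---|---|---|
| 2 g/day | 8% | 20% |
| 3 g/day | 50% | 50% |
| 5 g/day | 96% | 86% |
| 8 g/day | 100% | 98% |

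For orientation, a 5 g median is 45 kcal, or 45/2,000 = 2.25% of a 2,000 kcal diet.

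**5. Reading the table.** The floor distinguishes adherent from unchanged patients poorly if median habitual intake of the class that counts is about 5 g/day or more, and much better if it is 2 g/day. The article does not say where its patients lie, and it does not say which class counts. The answer could therefore fall in any row.

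**The case against.** The strongest reply is that nothing here is established beyond a loose abbreviation. A reader might infer that the target is 3 g of total PUFA, that ordinary diets meet it, and that the arms therefore do not differ on PUFAs. The article does not support that chain.

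- **Total PUFA is only one reading.** In Sections 2.8 and 2.12 the word total belongs to dietary intake, not to a fatty-acid class. The Introduction ties the abbreviation to omega-3. On that reading target and rationale agree, and the 27 kcal argument does not apply. This stands: the text is ambiguous, not clearly wrong.
- **No habitual intake is given.** That ordinary diets meet the floor is an assumption, and the table runs from 8% to nearly everyone. This also stands.
- **A floor is not a cap.** With a handbook and access to a nutritionist, patients already above 3 g may still raise their intake. This stands, but meeting the floor would then not show that they had done so.
- **The trial tests one combined diet.** The fiber target is not in question, so a contrast between arms remains, and any two-component intervention leaves the separate effects unresolved. This stands and limits the harm.
- **Diaries are kept in both arms**, so the contrast can be measured. This helps, but only once the class to be coded is fixed.
- **The fatty-acid class may be in the handbook or full protocol.** That is possible. The article nevertheless gives the target, the rationale and two expansions of the term, and these do not agree as printed.

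**Conclusion.** The point holds as an inconsistency with a conditional consequence. The Abstract, the Introduction and Sections 2.8, 2.12 and 2.13.1 do not settle which fatty acids the 3 g/day floor covers. If it covers total PUFA, it amounts to 1.1–1.8% of an assumed 1,500–2,500 kcal/day, hard to square with a diet called rich in PUFAs. It may then separate the arms poorly on PUFAs and add little to the per-protocol definition. How poorly depends on an intake that the article does not report: about 8–20% of patients already at the floor at an assumed median of 2 g/day, 50% at 3 g and 86–96% at 5 g, under a lognormal model with CV 0.3–0.5.

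A reader might go further and infer bias or an invalid primary comparison. That does not follow. Randomization balances baseline intake in expectation, and the intention-to-treat comparison of the combined diet remains valid. The concern is diluted contrast, an unclear per-protocol set and interpretability.

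**What to change.** 1. Reconcile the Abstract, the Introduction and Sections 2.8, 2.12 and 2.13.1 on which fatty-acid class the target refers to. Use that class in the patient handbook and in the per-protocol adherence definition under Section 2.15.
2. From the baseline questionnaire and the food diaries already planned for all participants, derive omega-3 and total PUFA intake separately.
3. Report the between-arm difference in achieved fiber, omega-3 and total PUFA intake, so that readers can see whether the arms differed.
4. Adjust the microbiota and SCFA comparisons for baseline fiber and PUFA intake, for example as covariates in a linear model where the outcome allows.

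No target value is proposed, and no exclusion by baseline intake. The cost is a change of wording plus some extra coding and analysis of data that the trial already intends to collect. Recruitment and visits are unaffected.

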#### 2.13.9. Assessment of Postoperative Follow-Up and Recovery

Patients will be carefully monitored for any signs of anastomotic leak and surgical site infection symptoms (fever, leukocytosis, severe abdominal pain, etc.) within 30 days after surgery. Diagnosis of anastomotic leakage will be confirmed by radiological examination (CT scan or MRI), clinical examination, detection of serum biomarkers (CRP and procalcitonin), and post-operative endoscopy (if required). Post-operative surgical site infections will be assessed using the ASEPSIS score system. In addition, the recruited patients will be followed up for at least one year in order to evaluate recurrences of CRC, response to adjuvant therapy, and overall/disease-free survival.

Subjects will be followed up by phone every week during the intervention and for a month after surgery, and every month until the completion of the trial. Data collected from participants that withdraw from the study will be retained following the Office of Human Research Protections. No financial incentives will be provided to any of the participants.

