### 2.15. Statistical Methods

The analyses of this study will follow the intention-to-treat (ITT) principles. All statistical analyses will be performed with SPSS v.22.0 software (SPSS Inc., Chicago, IL, USA), considering a level of *p* < 0.05 as statistically significant. Normality of distributions will be assessed using the Shapiro–Wilk test. A descriptive analysis of the variables will be carried out with punctual estimation and a confidence interval for 95% of security, treating the continuous variables as means, standard deviation, or medians according to the distribution of the variable. Categorical variables will be presented in frequencies and percentages. Continuous variables will be compared by Student’s “t” test and by analysis of variance (ANOVA), depending on the existence of 2 or more groups in each comparison. The association between categorical variables will be analyzed using the chi-square test. Studies of correlations between the variables will be carried out using the Pearson or Spearman test based on the normality of the analyzed variables.

Per protocol analysis will be performed within participants that fulfill the intervention. This approach will be used only for the primary outcomes and will be treated as a secondary analysis. In the case of a relevant number of missing values, multiple imputation or pattern mixture models will be used.

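### Follow-up ends for anyone who drops out, with no distinction between stopping the diet and revoking consent, so the intention-to-treat analysis can lack the clinical outcomes it needs

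*Protocol article*

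**What the plan says.** Section 2.8 (Intervention) puts three rules in sequence. First, on leaving by choice: "Participants may withdraw or revoke consent at any time without giving explanations and without any prejudice to them". Second, on what happens next: "Individuals who drop out of the study will not undergo further follow-up or be replaced by new subjects". Third, on removal by the study team: "Subjects may be withdrawn if researchers/clinicians consider that the participant can no longer comply with all the requirements of the study"; possible harm from a procedure is given as a further reason. The same section foresees that "some patients might find it difficult to follow the nutritional recommendations".

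Section 2.12 says that neither patients nor staff are blinded. Section 2.13.9 sets the window for anastomotic leak and surgical site infection at 30 days after surgery, and Table 1 places both at that visit. On those who leave, section 2.13.9 says only: "Data collected from participants that withdraw from the study will be retained following the Office of Human Research Protections".

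Section 2.15 sets the analysis: "The analyses of this study will follow the intention-to-treat (ITT) principles". On gaps in the data it says: "In the case of a relevant number of missing values, multiple imputation or pattern mixture models will be used". A per-protocol analysis is added as a secondary analysis of the primary outcomes only. Section 2.11 raises 48 patients per group to 54 to allow for 10% loss to follow-up.

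**The concern.** An intention-to-treat analysis compares the groups as randomised, whatever the adherence, and for that it needs outcomes on everyone randomised. Section 2.8 stops collecting outcomes when a patient drops out, and it does not say that stopping the diet is different from leaving the trial. The diet comes before surgery and the clinical outcomes come after it, so leaving during the diet period removes leak, infection, length of stay and 12-month status together.

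Retaining data already collected does not help, because these outcomes have not yet occurred. A later analysis plan cannot help either, since it cannot recover what the protocol told the site not to collect. If those who leave differ in leak risk and leave more often from one arm, the comparison of the remaining patients is no longer protected by randomisation.

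**Working it through.** **1. The timing.** The diet runs for 4 weeks before surgery (sections 2.8 and 2.10). Leak and infection are assessed from surgery to day 30 (section 2.13.9). A patient who drops out during the diet, and is followed no further, therefore has none of these outcomes, even though the operation may still take place in the same unit.

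**2. The plan's own allowance.** Section 2.11 gives 48 per group and 10% loss: 48 / 0.90 = 53.3, rounded up to 54. This reproduces. The allowance is 54 − 48 = 6 patients per group, so the sample size already treats leavers as lost to the analysis. (The 48 itself is close to a one-sided 5% calculation, which gives 49, against 62 for a two-sided one. Sidedness is not stated. That is a separate matter and does not enter here.)

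**3. Worst-case bounds on the leak difference.** Inputs: 54 randomised and 6 lost per arm, with the planned 30% and 10% rates (section 2.11) in the 48 who remain.
- Leaks among those observed: control 0.30 × 48 = 14.4; diet 0.10 × 48 = 4.8.
- All 6 lost diet patients leak and no lost control does: diet (4.8 + 6) / 54 = 20.0%; control 14.4 / 54 = 26.7%; difference 6.7 points.
- The reverse: diet 4.8 / 54 = 8.9%; control (14.4 + 6) / 54 = 37.8%; difference 28.9 points.

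The planned difference is 20 points. The interval shows what the lost patients could hide. It does not forecast bias.

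**4. Could losses of this size decide the result?** This is an illustration with assumed counts: 16 of 54 controls leak, 5 of 48 observed diet patients leak, and 6 diet patients are lost. Adding the lost patients back, with k of the 6 leaking, compares 16/54 with (5 + k)/54. The chi-square p-value without continuity correction is 0.007 for k = 0, 0.034 for k = 2, 0.064 for k = 3 and 0.27 for k = 6. Three unobserved leaks are enough to cross 0.05.

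**5. Is the direction known?** Suppose the diet has no effect (30% in both arms), 10% leave the diet arm only, and leavers have leak risk r. The observed diet-arm rate is (0.30 − 0.10 × r) / 0.90.
- r = 20%: 0.28 / 0.90 = 31.1%, against the diet.
- r = 30%: 30.0%, no bias.
- r = 40%: 28.9%.
- r = 60%: 26.7%, a spurious benefit of 3.3 points.

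The sign depends on r, which the document does not give.

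**The case against.** Four points can be made for the plan, and each has some force.

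- **Missing data are provided for.** A reader might infer that the plan relies on a missing-at-random assumption. It does not say so, and it names pattern mixture models, which are meant for loss that is not at random. What remains is that either method fills in outcomes from assumptions the data cannot check, when the outcomes themselves could have been collected.
- **Non-adherence is not the same as leaving.** The per-protocol set in section 2.15 is defined as those who complete the intervention, which makes sense only if some non-adherent patients stay in the trial. Withdrawal by staff is also permitted rather than required. So a flat contradiction between sections 2.8 and 2.15, or an intention-to-treat analysis that is bound to become an analysis of completers, is more than the text supports. The text still gives the site no rule for keeping a patient who stops the diet.
- **The no-follow-up sentence may not cover patients withdrawn by staff.** It names those who drop out, and withdrawal by staff comes in the sentence after it. Covering both is the natural reading but is not stated. If it does not cover them, the protocol is silent on their follow-up. Voluntary dropouts are affected either way.
- **Controls carry burdens too.** All patients keep a food diary, give samples, take phone calls and avoid supplements. A reader might infer that loss will fall on frail diet patients and favour the diet. The document says nothing on leavers' frailty or leak risk, so that is not established.

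Consent must of course be respected: ending collection is proper for a patient who revokes it.

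**Conclusion.** The point holds in limited form. As written, section 2.8 can remove the 30-day and later outcomes of patients who only stopped the diet or were judged unable to comply, and the intention-to-treat analysis in section 2.15 is weaker for it. Selective loss is plausible because the trial is open and the extra dietary burden is in one arm. Neither its direction nor its size can be derived from the document.

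The 6.7 to 28.9 point range is an extreme bound under equal loss of 6 per arm and planned rates in the rest. The p-values and the no-effect example rest on assumed counts and risks. Together they show that losses at the level the plan itself allows for could change the conclusion.

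A reader might also want the per-protocol analysis replaced. The document does not support that: "Per protocol analysis will be performed within participants that fulfill the intervention" describes an analysis that is explicitly secondary, and how fulfilment is defined in each arm is ordinary content of an analysis plan.

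**What to change.** In section 2.8 and the consent form, separate three events: stopping or not following the diet, withdrawal by staff, and revoking consent to data collection. State that patients in the first two groups remain in follow-up for 30-day leak and infection, length of stay and 12-month status, and are analysed in the arm to which they were randomised. Only revoked consent ends collection. Keep the per-protocol analysis as the secondary analysis it already is.

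The cost is protocol and consent wording and some follow-up effort. The phone contacts in section 2.13.9 are already planned, and surgery takes place in one hospital unit, so leak and length of stay should be obtainable from its records. Infection is scored with ASEPSIS and may need active contact. Stool samples missed on the day before surgery cannot be recovered this way, so the microbiota part of the primary outcome is not repaired.

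Full follow-up may also show a smaller difference. If, as an assumption, 10% of diet patients leave and keep the 30% risk, the diet-arm rate becomes 0.9 × 10% + 0.1 × 30% = 12%, and the difference 18 points instead of 20. That is the effect an intention-to-treat analysis is meant to estimate.
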